##### Definition of non-response

Participants will be classified as non-responders if their CGI—Improvement (CGI-I) score is 3 or above OR if their OASIS score has not improved by at least 4 points.

#### Treatment integrity and acceptance

Participants will complete the Credibility/Expectancy Questionnaire (CEQ) [125] which is a widely used 6-item measure that assesses treatment credibility and expectancy, after the first treatment session. Participant adherence to each intervention will be assessed as the number of total sessions attended.

### Data analysis

#### Rationale for statistical learning approach

Our primary goal of identifying mechanistic non-response indicators that can be readily assessed in clinical practice requires a machine learning approach that has (as its end product) a single model that any clinician can easily understand and adopt. Whereas there is evidence supporting the potential relevance of all our candidate predictors for individual bivariate relationships with non-response, we do not yet know how to optimally combine them into a single model to maximize prediction accuracy. This is especially true for the CO_2_/VH reactivity measures, which are multimodal, including physiology, behavior, and self-report. It is unlikely that all of these measures will provide a unique predictive signal; it is very likely that some may be redundant, and others may constitute noise. We therefore require a data-driven method of variable selection that reveals the best subset of predictors. A traditional approach would be to use a generalized linear model (GLM) and a stepwise selection algorithm, in which model terms are iteratively added or deleted and the model is repeatedly refit until some information criterion settles into a local optimum. Numerous weaknesses of such stepwise selection have been noted [126] including model selection bias, which can exaggerate the apparent strengths of relationships [127, 128].

The essential problem is that, with or without variable selection, an ordinary logistic regression is very likely to overfit the data [129] (meaning the model is trained to predict sample noise, which leads to inflated estimates of how well the model predicts the sample it was trained on, at the expense of generalizability when predicting other samples). Thus, a statistical learning technique is required that can handle the potential for highly correlated covariates and discourage overfitting. In developing a statistical learning approach for our objectives, we are mindful of the tradeoff between prediction accuracy and model interpretability that exists within the large umbrella of machine learning approaches. Generally speaking, the approaches with the best prediction performance (e.g., stacked ensembles that blend a diversity of machine learners) are the most successful in revealing comprehensible mechanisms. This has led us to select regularized regression, using the elastic net penalty, as our primary approach.

The chief advantage of the elastic net [130] is that it is still a GLM, and therefore its model output is as easy to understand and interpret as any GLM. Importantly, elastic net regression functions just as a GLM would in terms of handling covariates. For instance, if CO_2_ reactivity is entered into the model alongside other predictors, its estimated regression coefficient will reflect its incremental contribution to the prediction, controlling for all other covariates. The only difference is that the optimization procedure that fits the model, in addition to maximizing the likelihood of the observed data, works to minimize the size of the model coefficients, which is variously referred to in the literature as penalizing, regularizing, or shrinking the coefficients. The elastic net penalty is a mixture of “lasso” (L1) and “ridge” (L2) penalties. The lasso component favors sparsity by allowing the coefficients of the least influential covariates to be shrunk to 0, effectively selecting them out of the model entirely, while the ridge component favors inclusivity by enabling highly correlated variables to be shrunk together instead of arbitrarily picking one and discarding the rest. Importantly, in contrast to stepwise selection, variable selection is a by-product of coefficient shrinkage and the models are fit using all of the predictors. Cross-validation (tenfold) is used to tune the optimal combination and magnitude of penalties for a “just right” fit—flexible enough to capture real complexity, but constrained enough to avoid capturing noise—by choosing the amount of regularization that maximizes out-of-sample generalization instead of in-sample fit.

A potential disadvantage of the elastic net is that it does not provide an automatic search for potential nonlinear relationships or higher-order interactions among predictors, which other machine learning algorithms (e.g., random forests) would supply. However, in our publications and experience building machine learning ensembles to predict mental health outcomes [131], the elastic net has been the major workhorse of these ensembles, and the gains from adding other machine learners have been minimal at best (likely because the accurate capture of nonlinear, high-order interactions will require enormous sample sizes much larger than the ones we have worked with to date [132]). However, to assess how much loss of predictive accuracy an elastic-net may entail relative to more black-box approaches, we will also use superlearning/stacked ensembles, which have been touted as an optimal way to discover treatment rules that maximize response outcomes [133].

#### Model development and validation strategy

We will maintain the data collected at each site (UT and BU) as independent data sets. Two sets of models will be developed, one trained to each site’s data, which will then be used to predict the other site’s data. All statistical tests of model predictions will be performed using data from a completely independent sample. This ensures that findings are not merely “statistically significant” in the sense of being improbable under a null hypothesis, but also demonstrates real-world predictive utility by directly showing that predictions based on one clinical sample are likely to generalize to other clinical samples of the same population. We refer to the site used to fit models as the “train site” and the site used to validate models as the “test site”.

Hypothesis testing will be based on a series of model comparisons. All models will be fit to the train site and used to predict the probability of treatment response at the test site. These probabilities will be used to generate an ROC curve for each model’s ability to discriminate treatment responders from non-responders. Significant differences between curves will be evaluated using DeLong’s test for two correlated ROC curves as implemented by the R package “pROC”. The following model comparisons will be performed:All candidate predictors vs. excluding CO_2_/VH reactivity measures. This comparison addresses the question: do the novel measures of CO_2_/VH reactivity add predictive value beyond traditional—and easier to collect—measures like diagnosis or symptom severity? We hypothesize that the addition of the reactivity measures will significantly improve model performance. If CO_2_ reactivity is completely confounded with these competing predictors, then adding it to the model will not result in any predictive gains; CO_2_ reactivity can only improve model predictions if it provides unique information that is not captured by “confounders”.CO_2_ vs. VH reactivity. Finally, if the above model demonstrates the value of collecting CO_2_ reactivity measures, we will next assess does CO_2_ reactivity specifically predict treatment non-response (by revealing something about the underlying biology), or is it merely heightened sensitivity to the physiological sensations that are common to both CO_2_ inhalation and hyperventilation? Qualitatively, if VH reactivity has no predictive utility, then the statistical learning algorithm will have penalized these measures out of the model entirely by this point. However, the hypothesis of mechanistic specificity will be more formally tested by comparing a model that includes just CO_2_ reactivity measures to one that includes just VH reactivity measures. Note that the ability to perform a head-to-head comparison like this is one of the advantages of comparing ROC curves in an independent test set; the models do not need to be nested as they would when performing likelihood ratio tests on model fits.

Two strengths of this validation strategy should be emphasized. First, the significance of the biomarkers will be determined by their ability to outperform self-report measures, not just that their coefficients are significantly different from zero. The former speaks to their real-world utility; the latter does not. Second, the biomarkers are being compared on their ability to predict new data, not just their ability to fit the same data. This design/analytic feature helps ensure that we do not propagate failure-to-replicate issues. If we do not replicate a simplified model across sites and our hypotheses are not supported by the data (and there is not support for an alternative model with adequate sensitivity and specificity), we will recommend to the field that reactivity to CO_2_ and/or VH challenge (and the confounder variables we assessed) should not be used for determining patients’ suitability for EBT. Our use of a replicated assessment and a large sample helps instill confidence in these recommendations.

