**Methods:**

We will assess CO_2_ reactivity in 600 adults meeting criteria for one or more fear- or anxiety-related disorders prior to providing open exposure-based therapy. By incorporating CO_2_ reactivity into a multivariate model predicting treatment non-response that also includes reactivity to hyperventilation as well as a number of related predictor variables, we will establish the mechanistic specificity and the additive predictive utility of the potential CO_2_ reactivity biomarker. By developing models independently within two study sites (University of Texas at Austin and Boston University) and predicting the other site’s data, we will validate that the results are likely to generalize to future clinical samples.

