#### Translating anticipated ROC gains into clinical impact

The comparison of the ROC model curves is a framework for hypothesis testing, but the model will ultimately need to be couched in other terms besides an improvement in the ROC to convince clinicians of its practical utility, which depends not only on the improved performance of the model, but also clinical judgment about the optimal tradeoff between sensitivity and specificity: one can always boost the gain in the correct number of non-responders at the cost of increasing the number of falsely identified non-responders, and individual clinicians and patient circumstances may dictate different cut points. Thus, a metric like ROC that captures the overall tradeoff between specificity and sensitivity across all possible decision thresholds is the best way to frame our minimal objective, keeping in mind that this is a conservative expectation; larger predictive gains are possible.

However, assuming the minimal gains in ROC performance that we used to determine sample size requirements, we can offer a working example for one potential cutoff: if we were to require greater than an 80% predicted probability of non-response to forego a trial of EBT, then, out of 5000 patients entering treatment, the standard baseline model would only identify 4 true non-responders and falsely identify 1 responder as a likely non-responder. In contrast, the addition of CO_2_ reactivity measures would identify 262 true non-responders while misidentifying 26 responders as non-responders. This would spare > 10% of non-responders from an unsuccessful trial of EBT vs. < 0.2% under the baseline model, while incorrectly excluding only 1% of would-be responders. The biomarker assessment burden in our protocol is a single session, balanced against 12 one-hour sessions of treatment. The ability to spare 1/10 non-responding patients from the burden of unsuccessful treatment, while only negatively impacting 1/100 responding patients, justifies the burden of a single assessment session, in our opinion.

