#### Statistical power

We ran 5,000 computer simulations of our study design under a wide range of total sample sizes. In brief, a different multivariate distribution was defined for each of the following five diagnostic categories: (1) PD(with or without agoraphobia), (2) SAD, (3) GAD, (4) OCD, and (5) PTSD. Data were simulated to match the disorder-specific response rates (PD = 0.53, SAD = 0.45, GAD = 0.47, OCD = 0.43, PTSD = 0.59) reported in a meta-analysis of 87 studies [135]. The specified *N* for a given simulation was divided equally across the 2 sites and 5 disorder groupings within sites, and random samples of size *N*/10 were drawn for each disorder group for each site, one of which was arbitrarily labeled “train” and the other “test”. Just as we specified in our analytic plan, elastic-net logistic regression models were fit to the train site, and the optimal penalty mix (parameter alpha) and magnitude (parameter lambda) were selected using the average of 10 repeats of a tenfold cross-validation procedure. We then used this model to predict the response at the test site. These predictions (which are individual probabilities of response) and the actual response values were then used to generate ROC curves for the different models to be compared. The control model, which includes only “traditional” self-report measures, was assumed to have a true AUC of 0.63, and the experimental model, which adds CO_2_ and hyperventilation reactivity measures, was simulated to have a true AUC of 0.73. These values and their differences correspond to our minimal effect size of interest.

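### The only added-value test adds CO2 and VH reactivity together, but a win is read as the value of CO2; CO2's own increment is never tested.

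*Protocol article*

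**What the plan says.** The Abstract (Methods) states the aim: "we will establish the mechanistic specificity and the additive predictive utility of the potential CO_2_ reactivity biomarker".

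Under Model development and validation strategy, the protocol article lists two comparisons of ROC curves at the test site.

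- Comparison 1 is "All candidate predictors vs. excluding CO_2_/VH reactivity measures". Its question is put jointly: "do the novel measures of CO_2_/VH reactivity add predictive value beyond traditional" measures. The explanation that follows speaks of CO2 only: "CO_2_ reactivity can only improve model predictions if it provides unique information that is not captured by" the competing predictors.
- Comparison 2 is conditional on comparison 1: "if the above model demonstrates the value of collecting CO_2_ reactivity measures, we will next assess" whether the prediction is specific to CO2. It is done by "comparing a model that includes just CO_2_ reactivity measures to one that includes just VH reactivity measures".

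The first key hypothesis, in Sample size and data analytic approach, is worded neutrally, as the added value of reactivity measures. The second sets a model without VH against a model without CO2.

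Statistical power confirms what the 0.73 model contains: "the experimental model, which adds CO_2_ and hyperventilation reactivity measures, was simulated to have a true AUC of 0.73". The worked example under Translating anticipated ROC gains into clinical impact describes the same gain as CO2's: "the addition of CO_2_ reactivity measures would identify 262 true non-responders while misidentifying 26 responders as non-responders".

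**The concern.** VH is the plan's control biomarker, chosen because it should not index orexin activity. In comparison 1 it sits inside the block whose success is then described as the value of CO2. A joint test can show that the two challenges together improve prediction. It cannot show which one does so, and no listed comparison sets control+CO2 against control.

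Comparison 2 answers a different question: whether CO2 predicts better than VH. If both carry part of the signal, comparison 2 may well be non-significant. Comparison 1 would then be the only formal result bearing on CO2, and the text invites the reader to take it as demonstrating CO2's added value. That is the first half of the Abstract's stated aim and the basis for asking clinics to run a CO2 challenge.

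**Working it through.** **Inputs from Statistical power.** Control AUC 0.63; all-predictor AUC 0.73; 300 train and 300 test patients; directional DeLong test at p < 0.05; CO2–VH correlations 0.03 to 0.25; response rates 0.53, 0.45, 0.47, 0.43 and 0.59 in equal groups, mean 2.47/5 = 0.494. Stated power is 92.2% for comparison 1 and 82.7% for comparison 2.

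**Signal size.** For binormal scores, d = √2 × z(AUC). This gives 0.469 for the control model and 0.867 for the full model. An independent reactivity block must then supply √(0.867² − 0.469²) = 0.729.

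**The plan's own figure.** With these scores known without error, comparison 1 has 94.9% one-sided power (4,000 runs). With fitted models it is 93.6% to 94.5% one-sided, and a two-sided test gives 90.2% to 90.9%. The stated 92.2% lies between. The article does not give predictor counts or the covariance matrix, so exact reproduction is not possible. The 92.2% is not disputed, and the point does not rest on it.

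**Moving the signal.** Three simulations kept the AUC target and changed which block held the signal. Their assumptions are not in the document:

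- Simulation 1: elastic net; 10 control, 5 CO2 and 5 VH predictors; correlated within blocks; CO2–VH r 0.03–0.25; 400 runs (CO2 signal) and 200 runs (VH signal).
- Simulation 2: ridge logistic; 10 control, 4 CO2 and 4 VH predictors; 1,200 runs per scenario. VH-only results are for r = 0.03 / 0.15 / 0.25; the others are for r = 0.15.
- Simulation 3: ridge logistic; 4 CO2 and 4 VH predictors; uniform r 0.15–0.25; 800 runs.

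Share of runs significant, one-sided 0.05 (– means not available):

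| Contrast | Simulation | All signal in CO2 | All signal in VH | Shared equally |
|---|---|---|---|---|
| Comparison 1 (all vs control) | 1 | 93.6% | 92% | – |
| | 2 | 94.4% | 93.3 / 94.5 / 93.3% | 94.0% |
| | 3 | – | – | 94.4% |
| Control+CO2 vs control | 1 | 94.9% | 19% | – |
| | 2 | 97.3% | 1.1 / 3.9 / 8.1% | 83.0% |
| | 3 | – | 16–50% | 86.5–91.2% |
| All vs control+VH | 1 | – | 4.5% | – |
| Comparison 2, CO2 superior | 2 | 97.4% | 0% | 6.2% |
| | 3 | – | 0% | – |

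**Reading the table.**

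1. Comparison 1 wins equally often whichever challenge holds the signal. In simulation 1 the difference is 93.6 − 92 = 1.6 points, within the Monte Carlo error of 200 runs (√(0.92 × 0.08/200) = 1.9 points).
2. Control+CO2 versus control does discriminate, but its pass rate under a VH-only signal runs from 1% to 50% depending on the assumed covariances. CO2 can pass it by proxy.
3. With a shared signal, comparison 1 wins in 94.0% of runs and comparison 2 favours CO2 in 6.2%.
4. The power cost of the direct test is nil if CO2 holds the signal. If it is shared, the cost is 94.4 − 91.2 = 3.2 points at the least and 94.0 − 83.0 = 11.0 points at the most.

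Simulation 2 gives 97.4% for comparison 2 against the stated 82.7%, so its structure separates the two challenges more easily than the plan's own simulation did. Its individual percentages are illustrations.

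**The worked example.** Its percentages agree with the response rates: 5,000 × 0.506 = 2,530 non-responders, 262/2,530 = 10.4%; 5,000 × 0.494 = 2,470 responders, 26/2,470 = 1.05%. Only the label is in question.

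**The case against.** The strongest reply is that the plan claims something specific to CO2 only after comparison 2. The first hypothesis and the question put for comparison 1 are both joint. If VH held all the signal, the first hypothesis as worded would be true, and comparison 2 would expose the source: CO2 was declared superior in 0% of such runs, and VH came out ahead in 97–98% (simulation 2) and 87–95% (simulation 3). This stands. A reader might infer that the trial could end by naming CO2 the specific marker when VH does the work; the two-step plan does not allow that.

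Three further parts of the reply also stand.

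- The plan's named rival explanation is a sensitivity common to both challenges, not a VH-only effect. The VH-only case is a stress test, and the shared case is closer to the plan's own worry.
- A reader might infer that the worked example takes credit that belongs to VH. Statistical power says VH was given only a smaller relationship with outcome, by proxy through CO2, so in that simulation the gain comes essentially from CO2. The label is loose rather than materially wrong.
- A reader might infer that a comparison 1 win alone wrongly averts the negative recommendation. That recommendation covers CO2 and/or VH and depends on several joint conditions, so the documents do not support this.

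The argument that fitted coefficients would show where the weight lies is weaker. The plan itself prefers out-of-sample performance to coefficients as the standard for a biomarker.

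**Conclusion.** The concern holds as an attribution error with a missing contrast. Comparison 1 tests CO2 and VH jointly, the text reads a win as CO2's value and uses it as the gate, and nothing listed tests the CO2 increment that the Abstract promises. Because comparison 1 is significant in roughly 92–95% of runs whether CO2 or VH holds the signal, a win says nothing about which challenge earned it. That conclusion follows from the structure of the test; the percentages rest on assumed predictor counts and covariances.

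The error is confined to the added-value statement, the gate and the label on the worked example. The specificity claim is protected by comparison 2. This should be fixed, but it does not threaten the design, the data or the second hypothesis.

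**What to change.** 1. Add control+CO2 versus control as the test of CO2's added value and as the gate to comparison 2.
2. Report all predictors versus control+VH as CO2's increment beyond VH.
3. Keep all versus control for the first hypothesis, and word a win as a joint CO2+VH result.
4. Keep comparison 2, since CO2 can pass the new gate through its correlation with VH.
5. Re-run the existing power simulation for the new contrast, including a shared-signal scenario.
6. In the worked example, state that the 0.73 model includes VH measures, or recompute it for CO2 alone.

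Cost: wording, one simulation re-run and one or two extra DeLong tests. The second hypothesis, as worded, already requires the control+CO2 and control+VH models. No new data are needed. Power for the added-value test is about the same if CO2 holds the signal, and was 3 to 11 points lower in the simulations where it was shared.

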## Discussion

Anxiety-, obsessive–compulsive, and trauma- and stressor-related disorders reflect a significant public health problem. This study is designed to evaluate the predictive power of a novel biomarker based on a CO_2_ challenge, thus addressing the central question “can this easy-to-administer assay aid clinicians in deciding whether or not to initiate exposure-based therapy?”.

We hypothesize that the subjective and behavioral indices of CO_2_ reactivity will be the dominant predictors of EBT non-response. We do, however, include a set of competing predictors in our model. Hence, if our hypotheses are not supported and/or psychophysiological measures emerge as important predictors, we will still be able to deliver to the field an accounting of the variables/model that best predicts treatment failure. In essence, while our preliminary data provided a good basis to move forward, the work proposed in this application would comprehensively address possible confounders in a novel way. Ultimately, the final application of our work will be to recommend a specific assessment procedure and a specific go/no go assessment to guide clinical decisions for initiating exposure-based treatment vs. pursuing a different alternative.

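### The negative recommendation on CO2/VH reactivity can be averted by an undefined alternative model, judged on sites already used for testing and not required to beat the control predictors

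*Protocol article*

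**What the plan says.** All references are to the protocol article.

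- **Model development and validation strategy** sets the design: "Two sets of models will be developed, one trained to each site’s data, which will then be used to predict the other site’s data". It adds: "All statistical tests of model predictions will be performed using data from a completely independent sample". Two comparisons are fixed. The first is all predictors against all predictors without the CO2/VH measures. The second, made if the first succeeds, is CO2 measures against VH measures.
- The same section then gives the rule for a negative conclusion. It opens "If we do not replicate a simplified model across sites and our hypotheses are not supported by the data", adds in parentheses "and there is not support for an alternative model with adequate sensitivity and specificity", and concludes that CO2 and/or VH reactivity and the assessed confounder variables "should not be used for determining patients’ suitability for EBT".
- **Translating anticipated ROC gains into clinical impact** says of the decision threshold that "individual clinicians and patient circumstances may dictate different cut points".
- **Rationale for statistical learning approach** names one further model class: "we will also use superlearning/stacked ensembles". **Deriving treatment recommendation heuristics** names another, recursive-partitioning rules.
- The **Discussion** says that if the hypotheses fail, "we will still be able to deliver to the field an accounting of the variables/model that best predicts treatment failure".

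**The concern.** The negative recommendation has three joined conditions, and the third is open in four respects.

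1. **Model set.** The article does not say which models may count as the alternative.
2. **Criterion.** No value is given for adequate sensitivity and specificity, and no cut-off, although the article elsewhere treats the cut-off as movable and prefers the whole ROC curve for that reason.
3. **Data.** There are two sites and no third sample. By the time the hypotheses have failed, each site has been the test site once. A model adopted because the planned comparisons failed is no longer judged on data that played no part in choosing it.
4. **Comparator.** The section presents it as a strength that the biomarkers must outperform self-report measures. The parenthetical asks only for absolute sensitivity and specificity, so the increment over control is not required.

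At stake is the statement clinicians would use. The article aims at a web calculator, decision rules and a go/no-go assessment for starting exposure therapy. A trial in which CO2/VH reactivity adds nothing could end without the planned statement that it should not be used.

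**Working it through.** **The plan's own figures.** The clause has no figure attached. The nearest is the 92.2% power in Statistical power (AUC 0.73 against 0.63, 300 train/300 test, directional DeLong test, p<0.05). It cannot be reproduced exactly because the correlation between the two AUCs is not given. With Hanley–McNeil standard errors, one-sided power is 91.0% at correlation 0.4 and 94.7% at 0.5, so the figure is plausible and is not in dispute.

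**Inputs from Statistical power.** Mean response rate = (0.53 + 0.45 + 0.47 + 0.43 + 0.59)/5 = 0.494. A test site of 300 then has about 148 responders and 152 non-responders. The control model's true AUC is assumed to be 0.63.

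**Check A: can control predictors alone meet the criterion?** The thresholds are assumptions, because the article gives none. For equal-variance binormal scores, separation d = √2·Φ⁻¹(0.63) = 0.469. At the balanced cut, true sensitivity = specificity = Φ(d/2) = 0.593. In simulated test sites (148/152, no reactivity signal), the chance that some cut gives both at or above a threshold is:

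| Threshold for both | Control-only model, AUC 0.63 | No-information model |
|---|---|---|
| 0.55 | 93% | 3.9% |
| 0.60 | about 40–42% | about 0.03–0.04% |
| 0.65 | 2% | 0% |

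Taking 40% at threshold 0.60 and treating the sites as independent, either site succeeds with probability 1 − 0.60² = 64%, and both with 0.40² = 16%. The control signal is real here. The error is that it would hold back a verdict about CO2/VH.

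For k independent no-information models the chance is 1 − (1 − p)^k. With k = 20 this is 0.5% at threshold 0.60 (p = 0.00025) and 55% at 0.55 (p = 0.039).

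**Check B: can a noise reactivity model be picked out on test-site results?** This uses a stricter criterion than the clause states: beating the control model by one-sided DeLong at 0.05. Assumptions: 9 control predictors, one of them informative (control AUC about 0.62); 8 independent noise reactivity measures (the four CO2 and four VH indices of Table 1); 50.6% non-response; 300 per site; a lightly ridge-penalised score in place of the elastic net; 600 simulated trials.

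| Models examined | One direction | Either direction | Same model in both |
|---|---|---|---|
| Pre-specified full model | 0.5% | 0.8% | 0% |
| Any of 8 single-measure models | 16% | 29% | 0% |
| Any of 15 CO2 subsets (2⁴ − 1) | 12% | 21% | 0% |
| Any of 255 CO2/VH subsets (2⁸ − 1) | 29% | 49% | 0.3% |

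Repeating the 8-model case with a cross-validated elastic net (231 trials) gave about 16%, 29% and 0.4%. A further repeat gave about 18%, 33% and 0.3%. As a generic check, 8 one-sided tests at 5% give 1 − 0.95⁸ = 34% if independent, 22% at correlation 0.5 and 14% at 0.8.

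**The case against.** - **The parenthetical has a purpose, and this stands.** The recommendation also covers the confounder variables, which neither comparison tests. If reactivity adds nothing but the control model predicts well, removing the parenthetical would force the authors to call useful predictors unusable. Plain deletion is therefore not the remedy.
- **A reader might infer an unlimited search.** The article describes none. It speaks of an alternative model in the singular, names only ensembles and recursive-partitioning rules, and argues against stepwise selection. What the text supports is that the set is not bounded. The subset families in Check B are constructed for illustration.
- **A reader might infer that a chance model is likely to emerge.** That is not shown. A no-information model almost never reaches 0.60 on both measures, and a noise model rarely beats control in both directions. Replication across sites is the article's general aim, but the parenthetical does not require it.
- **A reader might infer that such a model would be reported as support for the hypotheses.** The text does not say so. The two tests stay as they are; the stated effect is only that the negative recommendation is not triggered. The Discussion's promise can be read as descriptive, and the study is presented as Stage 1.
- **Model lists, thresholds and multiplicity rules may sit in an analysis plan not shown.** Their absence from an article is no finding by itself. The finding is that the article prints a decision rule whose last condition lets evidence unrelated to the CO2/VH increment decide the CO2/VH conclusion.

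**Conclusion.** The point holds in a limited form. The printed rule lets a model that says nothing about the added value of CO2/VH reactivity, or one chosen on test-site results, avert the negative recommendation on that reactivity.

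The size is conditional. If beating control in one direction is enough, the false-success rate over 8 single-measure noise models is roughly 16–18%, and 29–33% if either direction counts. It is under 1% if the same model must succeed in both. If absolute sensitivity and specificity of 0.60 at some cut were enough, the control predictors alone would qualify at a single site about 40% of the time. These figures rest on the assumed thresholds, number of models, independent noise measures and binormal scores. The protocol fixes none of the quantities that decide between the low and high ends.

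**What to change.** In Model development and validation strategy, split the recommendation in two.

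1. **CO2/VH reactivity.** Let this statement depend only on the two pre-specified comparisons.
2. **Confounder variables.** Make this statement separately, from the control model's own performance when trained at one site and tested at the other.

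Label any other alternative model, and the best-predicting model promised in the Discussion, as exploratory, needing validation in new data and unable to change statement 1.

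If an alternative route is to be kept, list the models and the required sensitivity and specificity before test-site data are opened. Fix the cut-off at the train site, and require the same model to beat the control model in both site directions, with Holm adjustment across the list.

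The cost is protocol and analysis-plan wording; no data collection or sample size changes. The downside is that a post-hoc model from this trial can be reported only as hypothesis-generating.
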